**Figure 3 F3:**
[figure not shown]
Illustration showing how patients contribute to different groups for the characteristic comparisons during their time in the study. The blue arrows represent individual patients; the stars represent the date the index OAC was commenced; X represents the patient leaving the study. The boxes describe which group the patient will contribute comorbidity data to for that period (OAC will be subdivided to warfarin or direct oral anticoagulant, depending on which was prescribed). OAC, oral anticoagulant.

#### ​Objective 4: to describe persistence with DOACs compared with warfarin

Duration of prescribing of DOACs will be compared with warfarin using Cox proportional hazards, stratified by DOAC and adjusted for age and other important covariates identified in objective 3. All incident OAC users will be included. Time on OAC will be calculated as the difference between the discontinuation date of the OAC and the index date, as defined previously. Patients will be censored at the outcome (discontinuation of OAC therapy), on the date they stop contributing research standard data or the date of death.

All analyses will be conducted in STATA V.15.^24^ All values will be reported with 95% CIs.

#### 
*​*Missing data

There is likely to be a substantial amount of missing data for weight, BMI, smoking status and alcohol consumption as these variables may not be regularly updated by GP practices. We will use logistic regression to ascertain whether other variables (age, sex or comorbidities) predict whether these data are missing. If these variables do not predict the missing data, then we will assume that the data are missing at random. The proportion of missing data for these variables will be presented. If the data are missing at random, we will impute the missing values using multiple imputation and conduct a sensitivity analysis to investigate the effect of the missing data on the results of the analyses. However, previous studies suggest it may only be appropriate to impute weight and BMI.^25 26^

## 
*​*Patient and public involvement

Patients and the public were not involved in the production of this protocol or in the design of the study.

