## Introduction

A large body of evidence has shown that vitamin K antagonists (VKAs) are safe and effective for stroke prevention in atrial fibrillation (AF), but they have frequently been underused in older people.^1^ Reasons cited by physicians as making them less likely to prescribe VKAs for a person with AF include advancing age, risk of falls, comorbidities and previous bleeding.^2^

The first direct oral anticoagulant (DOAC), dabigatran, was marketed throughout Europe and in the UK in 2008, but was not licensed for stroke prevention in AF until 2011. Since then, three additional DOACs have been licensed for prevention of stroke: rivaroxaban, apixaban and edoxaban, and these are recommended in national and international guidelines as an alternative to warfarin.^3–5^ In the UK, the National Institute of Clinical Excellence (NICE) produces technology appraisals making recommendations for new medicines. The National Health Service is legally obliged to fund those medicines recommended by NICE within 3 months of publication of the appraisal. NICE published favourable technology appraisals for dabigatran and rivaroxaban in 2012,^6 7^ apixaban in 2013^8^ and edoxaban in 2015,^9^ meaning DOACs were available across the UK from mid-2012 onwards for stroke prevention in AF.

DOACs may allay some prescribers’ concerns when deciding whether to anticoagulate their older patients: they have fixed dosing schedules and can be added to compliance aids. They have also been shown in clinical trials to have a significantly lower risk of intracranial haemorrhage than warfarin^10–13^ (a prominent concern in patients with a history of falls).^14^

Since the introduction of DOACs, the overall rate of oral anticoagulant (OAC) initiation has increased by 58%.^15^ However, it is not known whether the introduction of DOACs has changed the rates of OAC prescribing for older people (aged ≥75 years) or how patient demographics, comorbidities and concomitant prescribing affect the choice of anticoagulant prescribed in UK general practice.

This study aimed to characterise prescribing of OACs to people aged ≥75 years in UK general practice, before and after the introduction of DOACs.

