### Objectives

To describe changes in the point prevalence and incidence of OAC prescribing by year prior to the introduction of DOACs (2003–2007), between the introduction of DOACs and the time they were recommended by NICE for stroke prevention in AF (2008–2012), and following NICE recommendation (2013–2017).To describe switching between OACs during the study period.To compare the characteristics of patients with AF who were newly started on OACs during each period described in objective 1 to those who were not prescribed anticoagulation in the same period.To describe persistence with DOACs compared with warfarin.

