### Source population

The study period will start on 1 January 2003 and will end on 27 December 2017. The source population will consist of all patients in CPRD who have ≥1 Read codes for AF and have contributed a minimum of 12 months’ research standard data prior to entry into the cohort. To be eligible to join the study, patients need to have the following: a Read code for AF recorded during or any time prior to the start of the study period; evidence to support the diagnosis of AF, such as a second AF diagnosis at a later date, an echocardiogram or prescription for a rate limiting or antiarrhythmic medication in the 3 months before the AF diagnosis or anytime after; and age of ≥75 years at study entry.

Patients will enter the cohort at the latest of the following dates:

Start of the study period.First AF diagnosis.75th birthday.A year from the date they started to contribute research standard data.

Patients will be censored if they leave the practice, the practice stops contributing data, at their date of death or at the end of the study. For the incidence calculations and comparison of patient characteristics, patients will be censored when they are prescribed an OAC.

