#### ​Incident and prevalent users

Exposure status will be defined at cohort entry as

‘No OAC’, where the patient had at least a year free of OAC prior to study entry and does not receive an OAC during the study period.‘Incident OAC users’, where the patient had at least a year free of OAC prior to study entry then was prescribed an OAC during the study period.‘Prevalent OAC users’ if the patient received an OAC in the year prior to study entry.

Exposure status for incident OAC users will be stratified at the start of each study period to no OAC, warfarin or DOAC.

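### Objective 4 compares DOAC starters from the later years with warfarin starters from 2003–2017 and names no control for calendar time, leaving the hazard ratio open to confounding by era

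*Protocol article*

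**What the plan says.** Protocol article, Statistical analysis, Objective 4: the duration of DOAC prescribing is compared with that of warfarin by Cox regression, with this adjustment and analysis set: "stratified by DOAC and adjusted for age and other important covariates identified in objective 3. All incident OAC users will be included".

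Source population: "The study period will start on 1 January 2003 and will end on 27 December 2017". An incident user is one "where the patient had at least a year free of OAC prior to study entry then was prescribed an OAC during the study period", so a warfarin start in 2003 and a DOAC start in 2017 both enter the same model.

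Introduction: the first DOAC was marketed in 2008 but "was not licensed for stroke prevention in AF until 2011". After the 2012 NICE appraisals, "DOACs were available across the UK from mid-2012 onwards for stroke prevention in AF". Apixaban and edoxaban received their appraisals in 2013 and 2015.

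The Time periods section divides the cohort into 2003–2007, 2008–2012 and 2013–2017. The text for Objectives 1 and 3 uses these periods; the text for Objective 4 does not mention them.

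**The concern.** The article fixes both the analysis set and the source of the adjustment variables for Objective 4, and calendar time appears in neither. The Objective 3 covariates are demographics, lifestyle factors, risk scores, comorbidities, co-prescribing and consultation counts. Period is the layer in which they are reported; it is not one of them.

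The study's premise is that anticoagulant prescribing to older people may have changed when DOACs arrived. The Introduction cites a 58% rise in initiation and suggests that DOACs may ease prescribers' reluctance. If the kind of patient started, the readiness to stop or the recording of prescriptions also changed, early warfarin starters differ from later starters of either drug for reasons unrelated to the drug.

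The protocol supplies two possible routes:

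- Under OAC switching, the index drug ends when an alternative is issued before its expected end date. A warfarin-to-DOAC switch could not happen before DOACs existed. The text does not say whether a switch counts as the discontinuation event; if it does, early warfarin time lacks one route to the event.
- Warfarin end dates can be extended by INR results, which the protocol says are recorded inconsistently. Any change in that recording over the years would enter the comparison.

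At stake is the study's one adjusted drug-versus-drug estimate. The Discussion expects the results to inform later comparative studies.

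**Working it through.** The protocol states no hazard ratio, event count or sample size for Objective 4, so there is no figure to reproduce. Three checks were made.

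**1. Dates.** The study period runs for 14.99 years. Years with almost no DOAC comparator: 2011 − 2003 = 8, or 2012.5 − 2003 = 9.5. If warfarin starts were uniform over the period (an assumption), the share preceding DOAC use in AF is 8/14.99 = 53% or 9.5/14.99 = 63%. Maximum DOAC follow-up is 7.0 years from 2011 or 5.5 years from mid-2012.

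**2. Size under an assumed drift.** Let the discontinuation hazard change by a proportion d per year for both drugs, let DOAC starts fall on average k years later, and let the true contrast at any given date be 1. Then the spurious HR ≈ (1 ± d)^k.

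| d | k = 4 | k = 6 |
|---|---|---|
| +2% | 1.02^4 = 1.08 | 1.02^6 = 1.13 |
| +5% | 1.05^4 = 1.22 | 1.05^6 = 1.34 |
| −2% | 0.98^4 = 0.92 | 0.98^6 = 0.89 |
| −5% | 0.95^4 = 0.81 | 0.95^6 = 0.74 |

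Both d and k are assumptions. On k: with uniform starts, the mean warfarin start is about 2010.5. The mean DOAC start is about 2014.5 (from 2011) or 2015.25 (from mid-2012), a gap of 4.0 to 4.75 years. The lower part of the 4–6 range is therefore the better supported.

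**3. Illustrative simulation, true HR 1.00.** Assumptions not in the documents: 70% warfarin with starts uniform over the study period; 30% DOAC with starts uniform from mid-2012; base discontinuation hazard 0.25 per year; other censoring 0.12 per year; the hazard changes at mid-2012 by the ratio shown. There was one run of 12,000 patients per scenario. In each cell the first value lets the hazard depend on the era of starting, and the second lets it change in calendar time during follow-up.

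| Later:earlier hazard | All starters pooled | Starts from mid-2012 only | Pooled, adjusted for the three periods |
|---|---|---|---|
| 0.67 | 0.72 / 0.74 | 0.99 / 0.98 | 0.86 / 0.91 |
| 0.8 | 0.87 / 0.87 | 1.00 / 1.01 | 0.96 / 0.99 |
| 1.0 | 1.04 / 0.97 | 1.05 / 0.96 | 1.05 / 0.95 |
| 1.25 | 1.18 / 1.13 | 1.03 / 1.01 | 1.08 / 1.03 |
| 1.5 | 1.32 / 1.26 | 0.97 / 1.01 | 1.07 / 1.04 |

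The row with no era effect departs from 1.00 by up to 0.05. That is run-to-run noise, and differences of that order elsewhere should not be read. Beyond it, pooling turns an era effect into an apparent drug effect in either direction, and restriction to contemporaneous starters removes it. Adjusting for the three periods removes most of it but not all, because 2008–2012 mixes years before and after DOACs could be used for AF.

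**The case against.** **The periods may already apply.** The Time periods section says in general terms that the cohort is analysed in three periods, and a fuller protocol may list more covariates than a condensed article can. This leaves some room for doubt. But the Objective 4 text states its population and adjustment source without mentioning the periods, and the periods would control era only partly.

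**Objective 4 is descriptive.** It comes last of four, with no stated hypothesis, and Objectives 1 to 3 are unaffected. That limits the weight of the point. An adjusted hazard ratio with a confidence interval is still a comparison and will be read as one.

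**Bias is not shown.** This stands. The documents give no persistence figure by era, and the 58% concerns initiation. The plan leaves the estimate exposed; it does not prove it wrong.

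A reader might infer more than the documents support:

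- *That follow-up of up to 15 years on warfarin against 5.5–7 years on DOACs itself biases the result.* It does not. Cox regression compares patients at the same time since initiation, and event times with only warfarin users at risk add nothing directly to the drug coefficient.
- *That drug and era cannot be separated.* Warfarin starts remain possible through 2017 (about 37% fall after mid-2012 if uniform), and this is why the fix works.
- *That Objective 3 cannot inform a DOAC-versus-warfarin model.* Its headline contrast is between patients "newly started on OACs during each period described in objective 1 to those who were not prescribed anticoagulation" and those same untreated patients, but Covariate classification, the Figure 3 legend and the strengths list all plan a split into DOAC and warfarin.
- *That stratifying by DOAC means stratifying the baseline hazard by the exposure, leaving no hazard ratio.* The natural meaning is results for each DOAC. The wording needs clarifying, no more.

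**Conclusion.** The point holds as one about exposure to bias. Followed as written, Objective 4 compares DOAC starters from about 2011–12 onwards with warfarin starters from all 15 years and names no control for calendar time, so its hazard ratio is open to confounding by era. Size and direction are unknown. The illustrative range of 1.08–1.34 (or 0.92–0.74) rests wholly on the assumed drift and gap, and with no drift there is no era bias. Saying that the estimate is confounded would go too far. The dates, the analysis set and the adjustment source come from the protocol itself, except that a few off-licence DOAC starts between 2008 and 2011 are possible. The rest of the study is unaffected, and the point merits correction because the remedy is cheap.

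**What to change.** State in Objective 4 that the main Cox comparison uses incident OAC users who started when both classes were available for AF, for example from mid-2012, and that it is stratified by or adjusted for calendar year of initiation. Within one initiation year, patients at the same time since starting are also at nearly the same calendar date, so the year term also handles changes during follow-up. It further allows for the later arrival of apixaban and edoxaban, which a single cut-off date does not.

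Fit one model with warfarin as reference and an indicator for each DOAC, and reword the phrase about stratifying by DOAC accordingly. Say whether a switch counts as discontinuation. Keep all 2003–2017 starters as a sensitivity or descriptive analysis.

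The cost is wording and a date filter on data already extracted. Earlier warfarin starters, and the few DOAC starts before the cut-off, leave the main hazard ratio, with some loss of precision. A cut-off at the start of 2013 would lose more DOAC starts than one at mid-2012. The loss is smaller than it looks, because initiation years without DOAC starters would add nothing directly to the drug coefficient in a year-stratified model.

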#### ​Objective 2: to describe switching between OACs during the study period

The number and percentage of patients switching from warfarin to DOAC, DOAC to DOAC and DOAC to warfarin will be calculated. The number of patients with multiple switches and details of the switches will be described. The average time to switch will be reported.

#### 
*​*Objective 3: to compare the characteristics of patients with AF who were newly started on OACs during each period described in objective 1, to those who were not prescribed anticoagulation in the same period

Demographics, characteristics, comorbidities and concomitant medications will be reported for the three time periods described. Prevalent OAC users will be excluded from this part of the study as we want to compare those started on an OAC with those who are not during each time period.

Patients may contribute data to more than one group, but they will be censored at the time they are prescribed their index OAC. For example, they may enter the study during the first time period but may not be prescribed an OAC until period 3. In this case, they would contribute data to the no-OAC group in time periods 1 and 2 and then one of the OAC groups in period 3. If they entered in period 1 and started on an OAC in period 2, they would contribute data to the no OAC group in period 1 and the OAC group in period 2; they would not contribute any data to period 3 as they would be censored. Figure 3 illustrates how patients contribute to different groups during their time in the study. Patient demographics (age and biological sex) and characteristics (BMI, smoking status and alcohol consumption) will be reported as percentages in predefined categories. The proportion of the cohort with each of the comorbidities and concomitant medications will be described. The mean CHA_2_DS_2_-VASc and HAS-BLED scores will be reported.

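### The missing-data rule reverses the missing-at-random condition: it triggers imputation when observed variables do not predict missingness and gives no action when they do

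*Protocol article*

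**What the plan says.** The rule is in the Missing data section at the end of Statistical analysis in the protocol article. It starts from an expected problem: "There is likely to be a substantial amount of missing data for weight, BMI, smoking status and alcohol consumption". It then has three steps.

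1. A diagnostic: "We will use logistic regression to ascertain whether other variables (age, sex or comorbidities) predict whether these data are missing".
2. A conclusion from a null result: "If these variables do not predict the missing data, then we will assume that the data are missing at random".
3. An action tied to that conclusion: "If the data are missing at random, we will impute the missing values using multiple imputation and conduct a sensitivity analysis".

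No step covers the case where age, sex or comorbidities do predict missingness. No threshold for prediction is given. The section promises to present the proportion missing, and adds a caution that "previous studies suggest it may only be appropriate to impute weight and BMI".

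The incomplete variables are used in two places. Under Objective 3, "characteristics (BMI, smoking status and alcohol consumption) will be reported as percentages in predefined categories". Under Objective 4, the Cox model for persistence is "adjusted for age and other important covariates identified in objective 3", so they enter it only if Objective 3 marks them as important.

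**The concern.** Missing at random (MAR) allows missingness to depend on observed variables; given those, it must not depend on the unseen value. Missing completely at random (MCAR) is the stricter case, in which missingness is unrelated to any data. Finding no association with age, sex or comorbidity is therefore what MCAR would look like. It neither defines nor establishes MAR.

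The consequence is practical. Imputation conditional on age, sex and comorbidity is useful when those variables predict missingness, and that is the branch for which the protocol plans nothing. The sensitivity analysis meant to show the effect of missing data hangs on the same condition, so it lapses there too. At stake are the reported distributions of BMI, smoking and alcohol by period and anticoagulant group and, less directly, the adjusted persistence comparison.

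**Working it through.** The protocol gives no figure to reproduce here: no missingness rate, cohort size or threshold. The check has a logical part and two illustrations on assumed inputs.

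**1. The two branches side by side**

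| Regression result | Compatible with | Protocol's action | Complete-case percentages |
|---|---|---|---|
| Variables do not predict missingness | MCAR; also missing not at random (MNAR) through the unseen value alone | Assume MAR, impute, sensitivity analysis | Unbiased if MCAR |
| Variables predict missingness | MAR or MNAR, not MCAR | None stated | Biased if the predictors also relate to the incomplete variable |

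Reading the protocol's term loosely as MCAR does not rescue the rule: imputation would still run where it corrects no bias and have no trigger where it could. In neither branch can a regression on observed variables separate MAR from MNAR.

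**2. How often the null branch would be reached**

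Assumptions: 30% missing, a binary predictor with 50% prevalence, a two-sided 5% Wald test. None of these is in the protocol.

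Power = 1 − Φ(1.96 − ln(OR) × √(n × 0.3 × 0.7 × 0.25))

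- n = 20,000, OR 1.1: √1,050 = 32.40; 0.0953 × 32.40 = 3.09; power 0.87.
- n = 50,000, OR 1.1: √2,625 = 51.23; 0.0953 × 51.23 = 4.88; power 0.998.
- OR 1.2: power about 1 at both sizes.
- 20 independent null tests: chance of at least one p < 0.05 is 1 − 0.95^20 = 0.64.

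**3. What is lost in the branch with no action: Objective 3**

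Simulation, 200,000 patients, 10 imputations. Assumptions: BMI falls 0.2 per year of age, comorbidity adds 1.0, residual SD 4.5. Missingness is logistic in age (log-odds per 5 years) and comorbidity (log-odds), with 30% to 35% missing.

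| Dependence (age, comorbidity) | Regression p | BMI < 20: true | Complete case | Imputed | Complete-case error in mean BMI |
|---|---|---|---|---|---|
| none (0, 0) | 0.32 | 6.45% | 6.45% | 6.42% | −0.01 |
| weak (0.3, −0.3) | < 0.001 | 6.62% | 6.19% | 6.58% | +0.12 |
| moderate (0.7, −0.7) | < 0.001 | 6.55% | 5.71% | 6.58% | +0.26 |
| strong (1.0, −1.0) | < 0.001 | 6.43% | 5.41% | 6.43% | +0.32 |

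The complete-case shortfalls are 6.62 − 6.19 = 0.43, 6.55 − 5.71 = 0.84 and 6.43 − 5.41 = 1.02 percentage points. Imputation is within 0.1 point throughout. In the first row, the only one in which the protocol calls for imputation, there was no bias to correct. The imputation model matched the model that generated the data, so this recovery is a best case.

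**4. Objective 4**

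A Cox model on 20,000 simulated patients, with BMI missing according to age and comorbidity (both in the model) at the moderate setting, gave:

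- full data: DOAC hazard ratio 0.811, SE 0.016;
- complete cases (n = 13,812): 0.814, SE 0.019.

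The estimate barely moves. The SE ratio, 0.019 / 0.016 = 1.19, is about what the smaller sample implies: √(20,000 / 13,812) = 1.20.

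**The case against.** Several points on the other side stand.

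- **The protocol does not say that imputation is withheld.** A reader might infer that the plan forbids imputation when predictors are found. It is silent on that branch. The inference is natural, because imputation is conditional on MAR and MAR is declared only after a null result, but it remains an implication.
- **Bias is not general.** A reader might infer that complete-case results are biased exactly where the rule fails to impute. That holds for the Objective 3 percentages only if the predictors of missingness also relate to BMI, smoking or alcohol. It does not carry over to the Cox model when missingness depends only on covariates in that model.
- **The reach is narrow.** Incidence, prevalence and switching use none of these variables. CHA₂DS₂-VASc does not use them either, and the HAS-BLED alcohol point is given on the presence of a record or code, so it does not turn on this rule.
- **The power figures measure how often a test fires, not bias.** They also assume a 5% threshold that the protocol does not set.
- **The document does not say why some patients are recorded.** It would be tempting to say that the complete cases are the sicker or more frequent attenders. The only reason offered is irregular updating by practices.

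The objection that an article condenses a fuller plan does not stand. The complaint is about a rule that is stated, not about detail left out, and no other section corrects it.

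**Conclusion.** The rule is wrong as written. The MAR condition is reversed, and the branch in which imputation is useful has no stated action. Under conventional significance testing in a large cohort, imputation and its sensitivity analysis would by implication seldom be triggered.

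The size of the harm depends on inputs that the protocol does not give. Under the assumptions shown, one BMI category is understated by 0.4 to 1.0 percentage points against a true value of about 6.5%. For Objective 4, if these variables enter the model, the loss is mainly precision, provided missingness depends only on model covariates and not on the outcome. The defect does not require imputation to become the primary analysis. It should be fixed, but it does not undermine the main prescribing results.

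**What to change.** Remove the test-based trigger and state the following instead:

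- MAR is an assumption, not the result of a test, and MNAR cannot be excluded.
- The logistic regression describes missingness and guides the choice of imputation-model variables.
- Weight and BMI, which the protocol itself regards as the likely candidates, are multiply imputed whatever the regression shows. The imputation model includes the predictors of missingness, anticoagulant group and period. For Objective 4 it also includes the outcome, for example the event indicator and cumulative hazard.
- Complete-case and imputed results are reported side by side.
- If smoking and alcohol are not imputed, their percentages are shown with the proportion missing and a note that they may be selective.

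Imputation is already planned, so the cost is revised wording and a small amount of extra analysis.
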